## Outcome measures

### Measures of feasibility

Feasibility of SHEPP in terms of recruitment, retention, and treatment fidelity will be assessed. *Recruitment* is defined as the percentage of participants enrolled out of the total participants who were invited at baseline. *Retention* is defined as the percentage of participants who will be available for follow-up at 10 months out of those recruited at baseline. *Treatment fidelity* will be defined as the proportion of planned physical activity sessions held [33]. The trial will be considered as feasible if recruitment, retention, and treatment fidelity are > 70% recruitment [34].

Measure of potential effect

Physical activity levels (in school, out of school, moderate to vigorous physical activity, and sedentary time) assessed by change in time (minutes) spent in physical activity. Dietary patterns in terms of percentage increase in fruits and vegetable serving/day, and percentage decrease in sweetened beverages and snacks/day, cardiometabolic risk factors by change in BP, BMI, and waist circumference (WC).

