## Recruitment

We aimed to recruit children from schools working under the AKESP, primarily because, all these schools have the same design of curriculum and extracurricular activities. There are 3 schools working under the AKESP and based on logistics, we decided to conduct SHEPP in 2 schools within 10-km distance from the study center. Approval was taken from the head of schools in AKESP. After these principals of both schools were approached and at least 2 detailed meetings were held to discuss the designing of the study and recruitment. List of children aged 9-11 years studying in the morning shift (in general class 2 and 3) were obtained from the principals, and 1280 students were assessed for eligibility. After this informed consent and assent forms were distributed in each class by the PI and research staff of both schools. A note was also written in their dairies so parents could understand about SHEPP. One-week time was given to parents to agree or disagree to consent. Parents were given contact numbers of PI in case they have any queries. The consent forms and assent forms were distributed to 1191 eligible parents and their children, out of which 1116 (93.7%) agreed to participate. In all, the total number of children recruited were 982 (82.5 %); 505 from school A and 477 from school B. Out of them, 496 (50.5) were boys. To improve recruitment and to maintain interest of the participants posters will be developed which will be posted in each class and in the corridors.

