## Data collection, management, and analysis

### Data collection

Data collection will be done by trained data collectors who will be trained by the primary investigator for (a) filling data collection forms, (b) measurement of blood pressure, waist circumference, height, and weight. Assessment of outcomes will be done at baseline and then after 10 months of intervention by the data collectors. Physical activity would be assessed using the validated youth physical activity questionnaire modified for children at baseline and follow-up [36]. Based on the findings of a previous pretesting and piloting study (unpublished), netball, rugby, skiing, snowboarding, sledging, skateboarding, and walk-the-dogs were excluded, as these are very uncommon activities and sports in our settings. However, some common traditional games such as Kabaddi (wrestling), Pahel dooj (hopscotch), Kho kho (game of chase), Pithu garam (dodge ball), kittening, bay blades, marbles, and activities related to ascending stairs were included. In addition, religious activities like performing prayer, recitation of Quran—the holy book, and household chores like sweeping, moping, cooking, dishwashing, and grocery purchase were incorporated. Finally, the modified version consists of 71 different activities in the same seven domains of the original YPAQ form. Physical activity will also be measured objectively using Mi wrist bands for at least 5% (*n* = 50) of the participants, to check the validity of physical activity measured by the questionnaire. Mi wrist band has shown 96% accuracy of measuring physical activity when compared to the gold standard [37]. Dietary assessment will be done using a 24-h dietary recall. Number of raw fruit and vegetables, number of sugar-sweetened beverages and snacks/day that are eaten will be recorded at baseline and follow-up. The dietary recalls will be conducted by trained staff on non-consecutive day. Blood pressure will be recorded using Omron m5 monitors using a pediatric cuff [38].. Weight would be recorded using Tanita’s digital weight scales. Community-setting aluminum scale was used to measure height with subjects standing barefooted (without head cover).

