#### Statistical analysis

Mean (SD) would be used for quantitative variables and frequency and percentage for categorical variables. Recruitment, retention, and treatment fidelity will be reported as percentage. Student *t* test would be used to compare quantitative variables (change in physical activity, BP, BMI, and waist circumference before and after intervention) between groups. Chi-square test to compare qualitative variables like percent increase in fruits and vegetables between the 2 groups from baseline to follow-up. Analysis would be done on intention to treat basis, that is, all participants will be analyzed in the same group as at time of allocation.

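### Intention to treat is defined as covering all participants, but the only test named for the quantitative secondary outcomes is a t test on change, which children without a 10-month value cannot enter

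*Protocol article*

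**What the plan says.** The Statistical analysis section sets both the test and the analysis set. A Student t test compares the two schools on "change in physical activity, BP, BMI, and waist circumference before and after intervention", and a chi-square test compares dietary percentage increase from baseline to follow-up. The analysis is declared to be by intention to treat, which the section spells out as "all participants will be analyzed in the same group as at time of allocation".

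The Data collection section gives the measurement times: "Assessment of outcomes will be done at baseline and then after 10 months of intervention". No intermediate assessment is described.

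The Measures of feasibility section defines retention as "the percentage of participants who will be available for follow-up at 10 months out of those recruited at baseline" and sets the success rule: "The trial will be considered as feasible if recruitment, retention, and treatment fidelity are > 70% recruitment". The Recruitment section gives the denominator: "the total number of children recruited were 982 (82.5 %); 505 from school A and 477 from school B".

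**The concern.** The gloss on intention to treat has two parts: everyone is analysed, and each child stays in the allocated group. The t test on change can honour the second part but not the first, because it needs two values per child. What would be run is a complete-case analysis by allocated school under a description that promises more.

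This matters because loss by 10 months could differ between two schools and could be related to activity or BMI. If so, a comparison of completers mixes the effect of the programme with the effect of who was still there to be measured. The Conclusion of the article makes large-scale replication depend partly on these potential effects, so readers should know which children the comparison contains.

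**Working it through.** **1. The denominator.** 505 + 477 = 982 recruited. Of those invited ("The consent forms and assent forms were distributed to 1191 eligible parents and their children"), 982/1191 = 82.45%, which agrees with the stated 82.5%.

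**2. Can the test use every child?** Change = 10-month value minus baseline value. With two assessments only, a missing 10-month value leaves change undefined. The Data management section has missing entries sent back to the data collectors for rechecking; that repairs incomplete forms but cannot supply a value for a child who was not seen. No other analysis of these outcomes is named. The dietary comparison from baseline to follow-up has the same restriction.

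**3. How many children?** Retention above 70% requires at least floor(0.70 × N) + 1 children.

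- Overall: 0.70 × 982 = 687.4, so at least 688 retained and at most 294 without a change score (294/982 = 29.9%).
- School A: 0.70 × 505 = 353.5, so 354 retained and 151 lost.
- School B: 0.70 × 477 = 333.9, so 334 retained and 143 lost.

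The article gives no expected retention. Over an assumed range, the number left out is about 49 at 95%, 98 at 90%, 196 at 80% and 393 at 60%.

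**4. What bias could follow?** Every input here except the recruited numbers is an assumption. If a fraction L of a school is lost, and lost children change g SD less than those retained, the completer mean exceeds the full-school mean by L × g. The bias in the difference between schools is (L1 − L2) × g. With the SD of change set to 1, SE = √(1/[505(1 − L1)] + 1/[477(1 − L2)]). With no true difference, the rejection rate of a two-sided 5% test is Φ(−1.96 + bias/SE) + Φ(−1.96 − bias/SE).

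Worked case, L1 = 30%, L2 = 10%, g = 0.5: bias = 0.15 − 0.05 = 0.10 SD; SE = √(1/353.5 + 1/429.3) = 0.072; rejection rate 28.6%.

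| Loss in the two schools | g (SD) | Bias (SD) | Rejection rate |
|---|---|---|---|
| 30% / 10% | 0.5 | 0.10 | 28.6% |
| 30% / 20% | 0.5 | 0.05 | 10.4% |
| 30% / 10% | 0.2 | 0.04 | 8.6% |
| 15% / 10% | 0.5 | 0.025 | 6.5% |
| 30% / 20% | 0.2 | 0.02 | 5.8% |
| 30% / 30% | 0.5 | 0 | 5.0% |

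The rates treat children as independent, which children taught in classes are not, and they leave aside the confounding of school with intervention. They isolate the effect of attrition and do not predict the trial's actual error rate.

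**5. Would a mixed model help?** It would where loss depends on the baseline value. A likelihood analysis then adjusts the 10-month mean for the baseline values of the lost children. In a simulation with an assumed baseline to follow-up correlation of 0.6 and baseline-driven loss of about 31% against 10%, completer bias was 0.10 SD and the likelihood estimate was off by about 0. The completer figure varies with how strongly baseline drives loss. Where the smaller change in lost children is not predicted by baseline, the model does not remove the bias.

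**The case against.** The strongest reply is that the sentence is about group membership only. The Adverse events section labels some children non-adherent or drop-outs, and the intention-to-treat sentence can be read as keeping them in their own school. A t test among children with both measurements, grouped by allocated school, would satisfy that reading. It is a possible reading, but it gives no work to the words about all participants. Nor does the article say whether a child who stops the intervention is still measured and analysed. During the study only one school receives the intervention, so that category can arise in one arm only.

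A second reply is that missing-data methods belong in an analysis plan, which is not shown. That stands: the absence of an imputation method is no fault here. The point is narrower. The article itself fixes a test and an analysis set that do not fit each other, and a later plan would still have to correct one of them.

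Two stronger readings are tempting and do not hold. A reader might infer that up to 30% of children will be silently dropped. The 70% figure is a success criterion, neither a forecast nor a cap, and the loss will not be hidden: retention is a primary outcome and "Recruitment, retention, and treatment fidelity will be reported as percentage". A reader might also take the 29% rejection rate as the expected size of the problem. It is one assumed scenario. It implies about 199 lost children (151.5 + 47.7), not 294, and with 30% loss in both schools and equal deficits there is no inflation at all.

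**Conclusion.** The point holds as a mismatch between the declared analysis set and the named test, confined to the secondary outcomes. At retention just above 70%, 294 of 982 children (29.9%) could not enter the t test; at 90% to 95% the number is about 98 to 49.

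The documents do not establish that bias will occur. It is nil if loss is unrelated to change, and also if loss and the deficit are the same in both schools. Across the unequal-loss inputs tried, it runs from 0.02 to 0.10 SD, with rejection rates of about 6% to 29% if children are treated as independent. Recruitment, retention and fidelity percentages are unaffected. The Limitations section already concedes weak internal validity from non-randomised allocation and a select group of schools; attrition would be a further source of bias, which that section does not mention.

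**What to change.** In the Statistical analysis section, make the main analysis of the quantitative secondary outcomes a likelihood-based mixed model of the baseline and 10-month values of all recruited children, with school, time and school-by-time as fixed effects and random effects for child and class. The school-by-time term is the same contrast in change that the t test targets, and a child with only a baseline value still contributes. State that the model protects only if data are missing at random given what was observed. Keep the completer t test as a sensitivity analysis, and compare baseline values of lost and retained children within each school.

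If the t test is kept as the main analysis, replace the reference to all participants with wording such as: *all children with 10-month data, by allocated school, including those who stopped the intervention*, and call it complete-case.

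Either change uses data already to be collected. The first costs a slightly more complex model and does not address the confounding of school with intervention. The second costs one sentence.

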## Methods: monitoring

Data monitoring will be done by random checks on the field site while data is being collected by the research staff. Additionally, a logbook will be maintained to log all the healthy heart educational sessions and physical activity sessions.

### Adverse events

During the exercise, any injury, vasovagal episodes will be noted down by the physical trainer and would be informed to the PI and the participant will be provided first aid in the school clinic. If needed the participant will be referred to a local area hospital and will be accompanied by the research staff to the hospital. Any cost will be borne by the investigators. If participants were unable to attend 3 sessions consecutively then they will be considered non-adherent. This will be noted in the logbook. Any participant who discontinues participating in the intervention will be considered as drop out.

## Ethics and dissemination

Ethical approval from the ethics review committee, Aga Khan University has been obtained (ERC number 2571-Med-ERC-13). Informed consent and assent have been taken from participants by the research staff. Confidentiality will be maintained while data is being collected by removing the identifiers.

## Discussion

Dietary behaviors, physical activity, and sedentary lifestyle are independent predictors of overweight and higher BMI among Pakistani primary school children [39]. From our previous non-randomized pilot study, we showed that such a physical activity program is feasible in girls’ schools and potentially beneficial to their BMI and BP [30]. The importance of the current study is that it includes both parents and teachers, who are of prime importance in the behavior adopted by the children. Furthermore, an interactive video and activity-based health education session is also incorporated in the SHEPP. Teacher training may be a key element for successful interventions. To overcome time constraints, a suggested solution is to integrate physical activity into daily routines and other areas of the preschool curriculum [40]. Additionally, parental barriers are associated with the time that children spend in both active and sedentary pursuits [41].

### Limitations

The limitation of this study is the lack of randomization, including a select group of schools. This might result in selection bias, thus limiting the internal validity of the study. Secondly, the objective measurement of physical activity through an electronic wrist band is done only for 5% of the population; however, using this on the entire population would not have been cost-effective. We have not used direct objective measures to test the knowledge of children before and after the intervention; however, we will measure indirectly the change in behavior by looking at their physical activity and dietary behaviors. Also, testing them on knowledge in addition to regular schoolwork might have reduced their interest in SHEPP. Another important limitation is that we could not convince the school authorities to incorporate the physical activity sessions 4 times a week due to lack of time slots during school time. However, we will try to compensate for this by introducing between class activity and physical activity in assembly. The Pax good behavior game will be implemented in a basic format and might not be implemented in an ideal setting due to lack of training resources.

## Conclusion

SHEPP is a unique health education program for children as it focuses on children while involving the parents and teachers into the behavior change process, if found feasible with potential positive effects on physical activity and dietary behaviors, we will replicate this on a large scale implementation study in public sector schools also.

## Data Availability

Data sharing does not apply to this article as no datasets were generated or analyzed during the current study.
